#### Reasons for (non)participation

Reasons for (non)participation will be collected in all invitees at baseline.

For the present study the Health Belief Model (HBM)[16] will be used as theoretical background to understand reasons for (non-)participation. This model is widely used to explain cancer screening adherence. The HBM states that health behaviour depends on an individual's desire to avoid illness and the belief that a specific action will prevent illness. Key factors in explaining health behaviour are: perceived susceptibility, perceived severity, self-efficacy, perceived benefits, perceived barriers. Reasons for (non)participation will be measured by eight items scored on a 4-point scale (e.g. "I think I have a higher chance of having colorectal cancer than other people my age..." [totally agree-totally disagree]. These questions are supplemented with 12 questions used in the first screening round (e.g. "I find that performing the FOBt is disgusting..." [agree – not agree].

#### Psychological consequences of a positive FOBt

Psychological consequences of screening will be documented in all invitees at baseline and immediately before and 2 weeks after undergoing colonoscopy in participants with a positive FOB test result.

The psychological consequences of receiving a positive FOB test result will be measured with the validated Dutch version of the 'Psychological Consequences of screening Questionnaire' (PCQ)[17]. The English version of this questionnaire has successfully been used in various screening studies[18]. The PCQ consists of three subscales: emotion (5 items), physical dysfunction (4 items) and social dysfunction (3 items). Scores on all items vary between 0 (not at all) and 3 (often) (e.g. "during the past week I had problems sleeping..." [not at all – often].

#### Burden of colonoscopy

The burden of undergoing a colonoscopy will be measured two weeks after the colonoscopy. Participants will be asked to rate on a 5-point scale the degree of embarrassment, pain and burden for one of several aspects of the colonoscopy procedure. Satisfaction with the procedure will be measured by 20 statements scored on a 4-point scale (e.g. "the endoscopist treated me with respect..." [not agree – agree ]. These 20 items-of-concern were developed from focus group sessions with patients regularly undergoing colonoscopies.

### Ethical approval

Ethical approval was obtained by the Committee on the Population Screening Act (WBO Committee).

### Data analysis

The primary goal of this second FOBt-based screening round is to assess the overall participation rate and to compare participation rates between groups (participants (1) and non-participants (2) to the first round and new invitees (3), within all three groups invitees will be randomized to receive a collection paper or not).

Group differences will be calculated using the Chi-square test. Descriptive statistics will be used to compare baseline characteristics of the subgroups.

To assess the effect of baseline characteristics and independent variables (assessed in the questionnaires) on the participation rate, multivariate analysis will be performed.

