### Study design and randomization

The study design is a cohort study examining the participation rate of a second round of FOBt screening. Within the cohort study a randomized controlled trial will be executed comparing the use of a collection paper versus no collection paper on the participation rate. All persons eligible for invitation are pre-randomized to one of both groups before informed-consent is obtained. Through randomization, non-responders to the previous round, responders to the previous round and first-time invitees will be equally distributed over both study groups.

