### Invitation procedure

Invitation will take place from August 2008 until June 2009. The screening program uses a centralized invitation procedure and all invitations will be sent out by the regional Comprehensive Cancer Centre Amsterdam. This institution is also involved in the organization of other population-based cancer screening programmes in the region including breast and cervical cancer screening. All persons will receive an invitation kit by postal mail containing an invitation letter, an information leaflet, an immunochemical FOBt, a test instruction and a frequently asked questions card. A collection paper to facilitate the collection of faeces will be enclosed in half of the invitation kits.

A reminder will be sent after two and eight weeks.

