### Sample size

In the first round 10.000 persons were invited for screening. Since we are focussing on the exact same group of persons, the number of persons that will be invited for the current study will also be 10.000.

Anticipating a 50% participation rate and the invitation of 10.000 eligible persons in the current study, the participation rate and its 95% confidence interval can be estimated. Assuming a participation rate of around 50%, the two-sided 95% confidence interval for the participation rate will extend 1% from the observed proportion, using the large sample approximation to the binomial distribution.

This sample size will allow us to detect differences of approximately 3% in participation rate between subgroups, with a continuity corrected chi-square test and a 0.05 two-sided significance level, requesting a power of 80%.

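### The collection-paper comparison is described as randomised within three first-round groups, but the only test named is an unstratified chi-square; this is valid, and gives up precision if uptake differs between the groups

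*Protocol article*

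**What the plan says.** The Study design and randomization section describes a cohort study with a randomised trial of collection paper against no paper inside it. The paper's effect on uptake is the first item under Secondary objectives.

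On allocation, Data analysis states that "within all three groups invitees will be randomized to receive a collection paper or not". Study design and randomization puts it less specifically: "Through randomization, non-responders to the previous round, responders to the previous round and first-time invitees will be equally distributed over both study groups". The ratio is 1:1: "A collection paper to facilitate the collection of faeces will be enclosed in half of the invitation kits".

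On analysis, Data analysis says: "Group differences will be calculated using the Chi-square test". Sample size also rests on a chi-square, with continuity correction, and on one overall rate: "Anticipating a 50% participation rate and the invitation of 10.000 eligible persons in the current study". Its conclusion is: "This sample size will allow us to detect differences of approximately 3% in participation rate between subgroups". No stratified test is named. A multivariate analysis of participation is planned for baseline and questionnaire variables, but the text does not say that it includes trial arm or first-round group, or that it serves the collection-paper comparison. Expected uptake in each of the three groups is not given anywhere.

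**The concern.** First-round status is known for every invitee before allocation and may well predict second-round participation. If allocation is balanced on it, the variation in uptake between the groups no longer contributes to the error of the arm difference. A crude chi-square still charges for that variation, because its standard error uses the total binomial variance. The test then rejects a true null hypothesis less often than 5% and detects a real effect less often than a stratified test on the same data.

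Efficiency is at stake, not validity. A small effect of the paper, below the 3 points used in planning, could be missed when the data already collected would have shown it.

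**Working it through.** **1. The plan's own figure.** Inputs from Sample size and Invitation procedure: 10,000 invitees, 5,000 per arm, uptake about 50%, two-sided 0.05, power 80%, continuity-corrected chi-square. For 50% against 53%:

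n per arm = [1.96·√(2 × 0.515 × 0.485) + 0.8416·√(0.25 + 0.2491)]² / 0.03² = 4,356, or 4,422 with continuity correction.

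Both are below 5,000. The smallest difference detectable with 5,000 per arm is 2.81 points uncorrected and 2.83 corrected. The stated figure of about 3 points is reproduced.

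**2. Assumptions for the comparison of tests (not in the documents).** Mix of prior responders, prior non-responders and new invitees 45/45/10%. Uptake either 75/25/50% or 85/15/50%; both give 50% overall. The paper effect is the same in each group, and allocation is stratified by group.

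**3. Formulas**, with n = 5,000 per arm:

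- Within-group variance: v = Σ w·p(1−p). For 75/25/50%: 0.45 × 0.1875 × 2 + 0.10 × 0.25 = 0.1938. For 85/15/50%: 0.45 × 0.1275 × 2 + 0.10 × 0.25 = 0.1398.
- SE used by the crude test: √(2 × 0.25/5,000) = 1.000 point.
- True SE under stratified allocation: SEw = √(2v/5,000).
- Crude size: 2·[1 − Φ(1.96/SEw)].
- Crude detectable difference: 1.96 × 1.000 + 0.8416·SEw.
- Stratified detectable difference: (1.96 + 0.8416)·SEw.
- Crude power at d: Φ((d − 1.96)/SEw). Stratified power: Φ(d/SEw − 1.96).

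| | 75/25/50% | 85/15/50% |
|---|---|---|
| SEw (points) | 0.880 | 0.748 |
| Crude test, true size | 2.6% | 0.9% |
| Crude detectable difference (points) | 2.70 | 2.59 |
| Stratified detectable difference (points) | 2.47 | 2.09 |
| Equivalent extra invitees (squared ratio − 1) | 20% | 53% |
| Power at 2.5 points, crude / stratified | 73.0% / 81.1% | 76.5% / 91.7% |
| Power at 3 points, crude / stratified | 88% / 93% | 92% / 98% |

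**4. Mild differences.** With shares 45/40/15% and uptake 60/40/47%, v = 0.45 × 0.24 + 0.40 × 0.24 + 0.15 × 0.2491 = 0.2414 and SEw = 0.983. Crude size is 4.6%. Detectable differences are 2.79 crude and 2.75 stratified. Power at 3 points is 86% for both.

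**5. Simple randomisation.** The crude SE of 1.000 is then the true one: size is about 5% and the detectable difference is 2.80 points. Adjusting for group still removes the between-group part.

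**6. Simulation check**, 40,000 replicates per scenario, shares 45/40/15%:

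- Stratified allocation: crude size was 4.7%, 2.9% and 1.1% for uptake 60/40/47%, 75/25/42% and 85/15/45%. Cochran-Mantel-Haenszel size was 5.0-5.1%. At a 2-point effect, power was 52% crude against 53%, 62% and 75% (crude 53% in the last case).
- Simple randomisation, 85/15/45%: crude size was 5.2%. Power at 3 points was 85% crude against 97% stratified; at 2 points it was 52% against 74%.

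**The case against.** Several points against the concern stand.

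- A reader might infer that the plan itself expects very different uptake in the three groups. It does not. Sample size uses one rate of about 50%, and comparing first-round participants with non-participants is a study objective. A large gap is plausible, but it is an assumption.
- A reader might infer that the true type I error is well below 5%. That needs allocation stratified by first-round group. Data analysis points that way, but Study design and randomization attributes the balance only to randomisation, which fits simple allocation too. Under simple allocation the size is about 5%.
- A reader might infer that the planned effect is at risk. At 3 points the crude test has 88-92% power under the assumptions in the table, and about 84% or more in every simulated scenario with continuity correction.
- A reader might set the crude 2.80 points against 2.09-2.47 and claim 29-79% more invitees (0.25/v − 1) alongside a conservative test. Those belong to different designs: 2.80 points and 29-79% to simple randomisation, conservatism to stratified allocation. With stratified allocation the gain is 20-53%.
- The test sentence follows a list of the three first-round groups and may be aimed mainly at comparing them with each other. A chi-square suits that comparison, and chi-squares run within each group would not be open to this variance argument. On either reading, no stratified overall test of the paper is named.
- The full protocol and SAP are not shown, and the planned multivariate analysis could include arm and group. Adjustment is often settled there. The article does, however, name a test and base its detectable difference on it, so commenting on that choice is fair.
- The arm comparison is a secondary objective, and an unstratified chi-square errs, if at all, on the side of caution.

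**Conclusion.** The point holds as one of efficiency. The article describes randomisation within first-round groups and names only an unstratified chi-square. That test is valid and delivers the stated 80% power at about 3 points.

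With stratified allocation and the assumed wide gaps in uptake, its true size is about 1-3%, and it detects 2.6-2.7 points where a stratified test would detect 2.1-2.5. If uptake hardly differs between the groups, nothing material is lost. If allocation is simple, the crude test is not conservative but still has less power than a stratified one when uptake differs. Which case applies cannot be settled from the documents. A stratified test is the better choice under both forms of allocation, and costs practically nothing where uptake is similar.

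**What to change.** In Data analysis, state that paper against no paper is compared with a Cochran-Mantel-Haenszel test and a stratified (Mantel-Haenszel) risk difference with 95% CI over the three first-round groups. Logistic regression with arm and group, reported as a standardised risk difference, would serve equally well. Keep the crude chi-square as a sensitivity analysis. In Study design and randomization, say whether first-round group is a stratification factor, so that the two sections agree.

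The cost is a sentence or two. First-round group is already known for every invitee, so no new data and no extra invitees are needed.

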**Methods and design:**

Two years after the first screening round, 10.000 average risk persons, aged 50 to 75, will again receive an invitation to participate in immunohistochemical FOBt (iFOBt) based screening. Eligible persons will be recruited through a city population database. Invitees will be randomized to receive either an iFOBt with a faeces collection paper or an iFOBt without a collection paper. The iFOBts will be analyzed in a specialized laboratory at the Academic Medical Centre. Positive iFOBts will be followed by a consultation at our outpatient clinic and, in the absence of contra-indications and after informed consent, by a colonoscopy. The primary outcome measure is the participation rate. Secondary outcome measures are the effect of the addition of a collection paper on the participation rate, reasons for participation and non-participation, measures of informed choice and psychological consequences of screening and measures of psychological and physical burden associated with the iFOBt and the colonoscopy. Another secondary outcome measure is the diagnostic yield of the program.

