#### Secondary objectives

• To evaluate the effect of the addition of a faeces collection paper to the iFOBt-kit on the participation rate;

• To compare participation rates between the first and second round;

• To compare the participation rates in groups that were defined as participants or non-participants in the first round;

• To evaluate the diagnostic yield (detection rates of cancer, high-risk adenoma and low-risk adenoma) and complication rate of iFOBt and colonoscopy and to compare these to results of the first screening round;

• To compare the baseline characteristics of participants and non-participants;

• To evaluate factors influencing the decision to participate;

• To evaluate invitees' ability to make a well-informed decision to participate;

• To evaluate participants' experience with the screening program in terms of their perception and the burden of the iFOBt;

• To evaluate the psychological impact on participants of receiving a positive test result;

• To evaluate the burden of the colonoscopy in iFOBt positives;

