### Study population

Our study population consists of 10.000 average risk persons between 50 and 75 years of age with the postal code of our target area. The target area of the second round is identical to the target area of the first round and is selected because it had an average uptake in the nationwide breast cancer screening program. Thus, among the invitees of the second round 3 different groups can be identified: 1) non-responders to the first round; 2) responders to the first round; 3) first-time invitees (persons aged 50–75 that moved into the target area or persons that turned 50 within the last 2 years).

Institutionalized people will be excluded from participation. Responders to the first round that tested positive in the first round and had a follow-up colonoscopy will not be re-invited. They will be advised follow-up conform the national guidelines on surveillance colonoscopy[12].

Other exclusion criteria are CRC symptoms in the last three months (rectal blood loss and/or changed bowel habits and/or unintentional weight loss). These symptomatic persons will be advised to contact their general physician and not to participate in the study. Also, persons with a life-expectancy of less than 5 years and persons that have undergone a colonoscopy in the previous 2 years will be excluded from participation.

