### Questionnaires

#### Socioeconomic and demographic characteristics

Baseline characteristics as age, marital status, education, employment and ethnicity will be recorded by a questionnaire two weeks after the invitation is sent.

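### Age is taken from a questionnaire and the participation model rests on questionnaire variables, although age, area, first-round group, arm and participation are held for all 10,000 invitees

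*Protocol article*

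**What the plan says.** Under Socioeconomic and demographic characteristics, the protocol article says: "Baseline characteristics as age, marital status, education, employment and ethnicity will be recorded by a questionnaire two weeks after the invitation is sent". The Data analysis section then says: "To assess the effect of baseline characteristics and independent variables (assessed in the questionnaires) on the participation rate, multivariate analysis will be performed". One secondary objective reads "To compare the baseline characteristics of participants and non-participants"; others concern the factors behind the decision and whether it was well informed. On coverage, the section on reasons for participation says: "Reasons for (non)participation will be collected in all invitees at baseline". The article gives no expected return rate for any questionnaire.

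The same article shows what is known without a questionnaire:

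- **Sampling frame** (Abstract): "Eligible persons will be recruited through a city population database".
- **Age and area** (Study population section): "Our study population consists of 10.000 average risk persons between 50 and 75 years of age with the postal code of our target area".
- **First-round group** (Study population): "among the invitees of the second round 3 different groups can be identified".
- **Arm** (Study design and randomization): every eligible person is allocated before consent is sought.
- **Participation** (Informed choice): defined by whether the test comes back, so it is observed for everyone invited.

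**The concern.** A comparison of participants with non-participants needs data from both. The article anticipates about 50% uptake, so about 5,000 invitees will not have returned a test. Participation is itself the return of a requested item, and the questionnaire falls at the same two-week point as the first reminder. It is therefore reasonable to expect fewer questionnaires back from non-participants.

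Three secondary objectives could be touched: the comparison of baseline characteristics, the factors influencing participation, and informed choice. Their results would describe people who answered a questionnaire, whereas the article means to learn about invitees and, in its Discussion, to use the factors found to improve future programmes. For age the loss is avoidable, because the selection of invitees already requires it.

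**Working it through.** **1. The plan's own figures (Sample size section).**

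- Interval half-width: 1.96 × √(0.5 × 0.5 / 10,000) = 0.0098, against the stated 1%.
- Detectable difference, for two groups of 5,000 (assumed here to be the two arms). Without correction, n = [1.96√(2p̄(1−p̄)) + 0.8416√(p₁(1−p₁) + p₂(1−p₂))]² / d². The continuity-corrected size is (n/4)[1 + √(1 + 4/(nd))]². For 50% v 53% this gives 4,356 and then 4,422 per group. At 5,000 per group the smallest detectable difference is about 2.8 points, against the stated figure of about 3%.

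Both reproduce. They apply to analyses of all invitees; the questionnaire-based comparisons have no stated size.

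**2. Who is analysed, and the informed-choice proportion.** From the article: 10,000 invitees, 50% participation. Assumed: the return rates, and informed choice in 70% of participants and 40% of non-participants. The true pooled proportion is then 0.5 × 70% + 0.5 × 40% = 55%. Observed proportion = (returned participants × 0.70 + returned non-participants × 0.40) / all returned.

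| Return, participants / non-participants | Returned, participants | Returned, non-participants | Participants' share of returns | Informed, among returns |
|---|---|---|---|---|
| 80% / 80% | 4,000 | 4,000 | 50% | 55.0% |
| 90% / 50% | 4,500 | 2,500 | 64% | 59.3% |
| 90% / 30% | 4,500 | 1,500 | 75% | 62.5% |
| 80% / 20% | 4,000 | 1,000 | 80% | 64.0% |
| 80% / 10% | 4,000 | 500 | 89% | 66.7% |

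Weighting by inverse return within participation status removes this shift. At 90% / 30%: (4,500 × 0.70/0.9 + 1,500 × 0.40/0.3) / (4,500/0.9 + 1,500/0.3) = (3,500 + 2,000)/10,000 = 55%.

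**3. Odds ratios.** Let rp1, rp0 be the return rates of participants with and without a characteristic, and rn1, rn0 those of non-participants. Then

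observed OR = true OR × (rp1/rp0) / (rn1/rn0).

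With an assumed true OR of 1.5 and equal return among participants (rp1 = rp0):

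| rn1 v rn0 | Observed OR |
|---|---|
| 20% v 20% | 1.5 |
| 80% v 75% | 1.4 |
| 50% v 40% | 1.2 |
| 30% v 20% | 1.0 |
| 25% v 15% | 0.9 |
| 15% v 25% | 2.5 |

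Return that differs only by participation leaves the OR at 1.5. So does return that also depends on the characteristic, if the ratio is the same in both groups: with rp 90% v 60% and rn 30% v 20%, 1.5 × 1.5/1.5 = 1.5. Bias needs the two ratios to differ.

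**4. What weighting can do for an odds ratio.** One weight for participants and another for non-participants cancel in the formula above, so the OR does not change. Adding area or first-round group to the weights removes only the part of the selection that those variables explain.

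**The case against.** The strongest reply is that this is mostly missing detail. An article may leave analysis sets and the handling of non-return to a fuller document, and recording age by questionnaire does not forbid taking it from the frame as well. The parenthesis in the Data analysis sentence can also be read as attaching only to the second group of variables. This stands as far as missing-data methods go. It does not cover the source of age, which the article names while also showing that a complete source exists.

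Four stronger readings are tempting, and the documents do not support them.

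- *Every predictor of participation depends on the questionnaire.* First-round group and arm are known for everyone, and the group comparison by Chi-square does not need it.
- *Non-participants who reply are a selected minority.* No return rate is given, nor how the questionnaire reaches invitees, and the article intends baseline collection from all of them. On the arithmetic they are a minority of non-participants only if fewer than half reply.
- *The associations will be biased or reversed.* Reversal needs particular assumptions. With uptake of 55% and 45% at high and low education, the true OR is (0.55/0.45)/(0.45/0.55) = 1.49. If participants return 90% throughout and non-participants 35% and 20%, it becomes 1.49/1.75 = 0.85. That follows from the chosen 1.75-fold ratio; other choices leave it unchanged or inflate it.
- *The database could replace the questionnaire, or weighting on it could repair everything.* Nothing shows that it holds education, employment, ethnicity, knowledge, attitudes or beliefs.

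**Conclusion.** The point holds in a limited form. Taking age from a questionnaire, and building the participation model on questionnaire variables, gives up complete data that the sampling frame and study records already contain. If non-participants return fewer questionnaires, the age comparison and the model describe responders only.

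The size cannot be fixed from the documents. Under the assumed return rates the pooled informed-choice proportion moves from 55% to between 59% and 67%; this requires return and the informed proportion both to differ by participation. Under the assumed unequal return among non-participants, a true odds ratio of 1.5 is observed anywhere from 0.9 to 2.5. The direction cannot be predicted, so a general caveat in the report would not tell readers which way to adjust.

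The participation rate, the collection-paper comparison and the first-round group comparison stand as planned. The matter is confined to secondary objectives, but it is cheap to put right.

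**What to change.** 1. Take age, postal area, first-round group (and first-round test, where held) and arm from the invitation and study records, and fit the main participation model on all invitees. Make the age comparison of participants and non-participants on the same set.
2. Weight the informed-choice proportion by the inverse probability of questionnaire return, modelled from the record-based variables separately in participants and non-participants. State that this assumes return is unrelated to informed choice given those variables.
3. For predictors held only in the questionnaire (education, employment, ethnicity, knowledge, attitude, beliefs), report return rates by participation status, give a sensitivity range for differential return using the formula in the working, and limit inference to responders. Weighting on database variables cannot remove selection on these variables themselves.

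The cost is some extra analysis and somewhat wider intervals for the weighted estimates. The record-based variables are already held, so no new data collection is needed.
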